Understanding whether exercise prevents or reverses frailty and sarcopenia, as well as the mechanisms implicated, is critical for improving health and quality of life in men with mPCa on ADT, yet the mechanisms by which exercise improves frailty and sarcopenia, particularly in the context of ADT, are unknown (7). Proposed mechanisms are improvements in systemic inflammatory and skeletal muscle tissue-related outcomes (7). Thus, we will investigate systemic inflammatory biomarkers associated with frailty [IL-6, TNF-α, C-reactive protein (CRP)] and muscle tissue-related outcomes associated with sarcopenia (myokine release and activation of insulin pathway-related biomarkers) to aid in refining explanations surrounding the frailty–sarcopenia–ADT axis with exercise (5, 24–29). In addition, exploring whether the effects of exercise are associated with biochemical cancer progression will provide insight into understanding the roles of exercise in long-term oncologic outcomes in the context of mPCa.

The overall objective of the FIERCE trial is to evaluate the efficacy of a 16-week multicomponent exercise intervention encompassing supervised, clinic-based circuit training utilizing resistance exercises and self-directed aerobic exercise on frailty and sarcopenia with an exploration of novel biomarkers at the intersection of frailty, sarcopenia, and disease progression. The primary outcome of this study is change in frailty score, measured by the Fried frailty phenotype (i.e., muscle loss, exhaustion, physical activity, gait speed, and strength) and frailty-associated biomarkers (IL-6, TNF-α, CRP). Secondary outcomes include change in sarcopenia status, measured using a computerized tomography (CT) scan and sarcopenia-associated muscle biopsy-driven biomarkers (myokines and insulin pathway markers). An exploratory outcome will assess how plasma from patients undergoing the exercise intervention affects prostate cancer cell proliferation (LNCaP cells). We hypothesize that the exercise group, compared with the attention control group, will exhibit the following: (1) a lower proportion of frail and pre-frail scores and improved individual scores of each frailty component; (2) improvements in systemic inflammatory biomarkers; (3) improved sarcopenia status; (4) increased gene and protein expression of muscle biopsy-driven anti-inflammatory myokines and insulin pathways; and (5) suppressed biochemical progression of PCa.

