###### Exhaustion

2.6.2.1.2

Exhaustion is assessed using the vitality score from the Short Form Health Survey (SF-36), a 36-item questionnaire assessing quality of life. A cut point of <50 for those 50–65 years and <40 for those >65 years is used to identify exhaustion = 1 point (36, 37, 41).

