###### Low physical activity

2.6.2.1.3

The Community Health Activities Model Program for Seniors’ physical activity questionnaire is used to assess physical activity, with low activity defined as <383 kcals = 1 point (36, 37). This is a 41-item questionnaire asking about time spent undertaking certain physical activities (42).

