###### Slowness

2.6.2.1.4

Usual gait speed is assessed over a 15-foot flat surface distance with an average time over two attempts of ≥7 s for participants ≥173 cm tall or ≥6 s for those <173 cm tall considered as “slow” = 1 point (36, 37). In addition, the participant is asked to walk at their “fast” pace for the 15-foot distance a further two times, but this is not utilized for the Fried frailty phenotype composite score.

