###### Weakness

2.6.2.1.5

The chair stand test is used to assess leg strength, where a time ≥12 s to complete five chair stands is considered weaker = 1 point (36, 37). Participants are asked to sit in a chair with their hands crossed over their chest. While keeping the feet flat and back straight, participants rise to a full standing position and then sit back down, repeating five stands as fast as they can.

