### Sample size calculation

2.11

We will enrol a total of 80 eligible participants. Considering a 10% attrition rate, the sample size of the analysis population will be 72. We plan to accrue participants for 24 months. The Wilcoxon rank-sum test will be used to compare the score based on the frailty phenotype (37) between the two groups for the primary analysis. Table 4 shows the anticipated distribution of the score in each group (59). With a sample size of 72, the study will have 84% to detect the relative effect of 0.30 at a 0.05 two-sided alpha level. This power calculation was performed by the WMWssp package (60). For comparing each of the five criteria of the frailty score (binary outcomes), the sample size of 72 will provide 80% power to detect a moderate effect size (Cohen's *h* = 0.415) at a 0.05 two-sided alpha level (61). For each continuous outcome, two-sample *t*-tests will be used for the between-group comparison as the primary analysis. Log transformation may be considered, if appropriate. With a sample size of 72, the study will have 80% power to detect a moderate to large effect size (Cohen's *d* = 0.67) at a 0.05 two-sided alpha level.

**Table 4 T4:** Sample size and power with the anticipated distribution of the frailty score (0–5).

Frailty status	Not frail (%)	Pre-frail (%)		Frail (%)			Total sample size	Relative effect	Power (%)
	0	1	2	3	4	5			
Attention control	15	63	17	4	1	0	72	0.30	84
Intervention	85	14	1	0	0	0			

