### Statistical analysis

2.12

This study will assess whether a 16-week, multicomponent exercise intervention will improve the frailty status of mPCa on ADT. Furthermore, we will assess the effect of the intervention on sarcopenia status, skeletal muscle-derived biomarkers, and cell proliferation rate.

A total of 80 eligible patients who complete the baseline assessment will be randomly assigned to the exercise or attention control groups in an allocation ratio of 1:1 using a permuted blocked design with varying block size (with investigators blinded to block size). The randomization will be stratified by frailty status (pre-frail vs. frail) at baseline assessment.

All analyses will be performed based on the intention-to-treat principle. We will repeat the same analyses with the subjects who complied with the protocol as secondary analyses. Baseline demographic and clinical measures, as well as baseline values of trial outcomes, will be presented by randomized intervention group; continuous measures will be summarized by mean (SD) or median (IQR) and categorical measures by frequencies (percent's). The randomized groups will be compared concerning baseline demographic and clinical variables using two-sample *t*-tests, Wilcoxon rank-sum tests, or Fisher's exact tests to confirm baseline comparability. These variables will be included in the adjusted analyses if clinically meaningful or statistically significant differences are identified.

The primary outcome is the score based on the Fried frailty phenotype (37), which consists of five criteria, and the score will take an integer value from 0 to 5. The Wilcoxon rank-sum test will be used as the primary analysis for comparing the score distribution between groups. Mean score and a corresponding 0.95 confidence interval (CI) will be calculated. We will also assess the intervention effect on each of the five criteria for the frailty phenotype for hypothesis generation purposes. For each, we will perform Fisher's exact test for the between-group comparison and estimate an odds ratio and a corresponding 0.95 CI. Regression analysis will be used to identify baseline factors associated with the outcomes, where proportional odds models will be used for the score as an ordered categorical variable with six categories, and logistic regression models will be used for each of the five criteria.

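### The only between-group test named for the frailty components is Fisher's exact test on 0/1 items, although four are measured on full scales; comparing the measured values would be more powerful, and the stated 80% power for the binary items is wrong

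*Protocol article*

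**What the plan says.** Sections 2.6.2.1.2 to 2.6.2.1.5 record four components as quantities and then cut each to a 0/1 point:

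- Gait: "Usual gait speed is assessed over a 15-foot flat surface distance with an average time over two attempts", with a cut in seconds that depends on height.
- Chair stands: "a time ≥12 s to complete five chair stands is considered weaker = 1 point".
- Vitality: "A cut point of <50 for those 50–65 years and <40 for those >65 years is used to identify exhaustion = 1 point".
- CHAMPS energy expenditure: "with low activity defined as <383 kcals = 1 point".

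Table 1 schedules the Fried measures at baseline and week 18. The first hypothesis in the Introduction predicts "a lower proportion of frail and pre-frail scores and improved individual scores of each frailty component".

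Section 2.11 treats the criteria as binary ("For comparing each of the five criteria of the frailty score (binary outcomes") and states 80% power at h = 0.415, two-sided 0.05, with 72 men. Section 2.12 calls the criterion analyses hypothesis-generating and gives the test: "For each, we will perform Fisher's exact test for the between-group comparison and estimate an odds ratio and a corresponding 0.95 CI". It adds logistic regression on the criteria to look for associated baseline factors.

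For continuous outcomes, section 2.11 gives a two-sample t-test with 80% power at d = 0.67. Section 2.12 gives t-tests, supporting Wilcoxon tests and identity-link mixed models for the other continuous outcome variables. Neither section lists the variables meant.

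**The concern.** The cut points are needed to build the 0-5 score. They are not needed to compare a single component between arms, and cutting a measured value discards information. A man whose chair-stand time falls from 20 s to 13 s has improved a great deal, yet scores 1 both times because the cut is 12 s.

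The component results are meant to show which domains exercise changes and to inform larger trials. If the named analysis often misses a real change in walking or chair-stand time, the report could suggest no component effect where one exists. The 80% stated for the binary criteria would make such a null result look more informative than it is.

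**Working it through.** **Inputs.** Section 2.11: "Considering a 10% attrition rate, the sample size of the analysis population will be 72". With 1:1 allocation this is taken as n = 36 per arm. Alpha is 0.05 two-sided. The targets are d = 0.67 (continuous outcomes) and h = 0.415 (binary criteria). Table 4 gives the anticipated score distributions.

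**1. The plan's continuous-outcome figure.** Noncentral-t power at d = 0.67 with 36 per arm is 80.1%. The stated 80% reproduces.

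**2. The plan's binary-criteria figure.** The arcsine formula is power = Φ(h·√(n/2) − z).

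- 36 per arm, two-sided: 0.415 × √18 − 1.960 = 1.761 − 1.960 = −0.199, so power is 42.1%.
- 36 per arm, one-sided: 54.6%.
- 72 per arm, one-sided: 0.415 × 6 − 1.645 = 0.845, so power is 80.1%.

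Of the variants tried (36 or 72 per arm, one- or two-sided), only 72 per arm with a one-sided alpha returns 80%. This suggests, without proving it, that the total was entered as the per-arm size with a one-sided alpha. With 36 per arm and a two-sided alpha, 80% needs h = (1.960 + 0.842)/√18 = 0.66. By exact Fisher enumeration at h = 0.415, power is 10% at 10% control prevalence and 27% to 32% at the control prevalences tried from 20% to 90%.

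**3. What cutting costs at d = 0.67.** Assume a normal outcome with equal SD and a pure shift. If a proportion p of controls meets the criterion, the exercise-arm proportion is Φ(Φ⁻¹(p) − 0.67). Two-sided Fisher power comes from enumerating every table with 36 per arm.

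| Control prevalence | Exercise prevalence | Fisher power | t-test on the measured value |
|---|---|---|---|
| 10% | 2.5% | 6.7% | 80.1% |
| 22.6% | 7.8% | 30.5% | 80.1% |
| 30% | 11.6% | 38.7% | 80.1% |
| 50% | 25.1% | 49.0% | 80.1% |
| 63% (maximum) | 36.8% | 50.0% | 80.1% |
| 90% | 73.0% | 36.0% | 80.1% |

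The 22.6% is the average item prevalence implied by the control row of Table 4: mean score 0.63 + 2 × 0.17 + 3 × 0.04 + 4 × 0.01 = 1.13, divided by 5 items.

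An uncorrected chi-square test on the cut value reaches at most 60.0%. At the best cut point, then, about 20 points are lost to cutting and about 10 more to the conservatism of Fisher's test.

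**4. Does the gap depend on using d = 0.67?** Two other targets in the plan, converted to a shift by Φ⁻¹(control) − Φ⁻¹(exercise):

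- h = 0.415 at 22.6% control prevalence: the shift is 0.65; Fisher 29%, t-test 77%. At 50% control prevalence: Fisher 31%, t-test 60%.
- Both rows of Table 4: the intervention mean is 0.14 + 2 × 0.01 = 0.16, or 3.2% per item. For 22.6% against 3.2% the shift is 1.10; Fisher 59%, t-test over 99%.

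The gap is 29 to 48 points in the first setting and about 40 in the second.

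**The case against.** The strongest reply is that these tests are declared hypothesis-generating and the primary analysis is the Wilcoxon test on the 0-5 score, so no confirmatory conclusion depends on them. That stands, and it limits the importance of the point. It does not make the choice a good one, because an analysis meant to generate hypotheses has most need of sensitivity.

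Second, section 2.6.2.1 defines each component score as 0 or 1, so a comparison of proportions tests the first hypothesis as worded. That also stands. The measured value answers a related but different question, which is why it should be added beside the Fisher test and not replace it.

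Third, a reader might infer that the plan rules out any continuous analysis of these four measures. The documents do not support that. The t-test rule in section 2.11 applies to each continuous outcome without exclusion, and a condensed article may leave the list of variables to a fuller document. The wording of section 2.12, which turns to other continuous variables after dealing with the score and its criteria, leans towards leaving them out but does not settle it.

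Fourth, d = 0.67 is the target for continuous outcomes, not for the criteria. The 50% ceiling belongs to that effect size: at Table 4's item averages Fisher reaches 59%.

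A reader might also infer that a man below the cut at baseline can contribute nothing. That is not so: controls may worsen across the cut while exercisers do not, and a week-18 comparison would capture it.

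**Conclusion.** The point holds as a matter of efficiency and clarity in secondary analyses. For four components measured on full scales, the one between-group test that is named is clearly weaker than the t-test the plan already uses elsewhere, and the article does not say whether that t-test applies to them. The loss is at least about 30 points of power at d = 0.67.

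The comparison assumes normality, equal SD, a pure shift, 36 men per arm and one common cut point; the gait and vitality cuts in fact vary by height and age. Skewed times or kcal would change the exact figures. The Table 4 averages spread the score evenly over five items, muscle loss included, so they illustrate the size of the loss and do not predict it for any one item.

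The error in the binary power statement needs none of the distributional assumptions: with 36 per arm, h = 0.415 gives about 42% by the arcsine formula, and about one third or less by the Fisher test the plan will use.

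**What to change.** In section 2.12, state that usual-gait time, five-chair-stand time, SF-36 vitality and CHAMPS kcal are also compared between arms at week 18 by the existing two-sample t-test, with mean difference and 95% CI, as the more sensitive component analysis. Use the Wilcoxon test or a log scale if the data are skewed, and adjust for baseline if preferred. Keep the Fisher tests and odds ratios alongside, keep both sets hypothesis-generating, and leave the 0-5 score and its primary test unchanged. If the general continuous-outcome rule was always meant to cover these values, one sentence saying so is enough.

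In section 2.11, cite d = 0.67 for the four measured values and correct the binary statement: about 42% two-sided power at h = 0.415 with 36 per arm, or h of about 0.66 for 80%. Say that both are arcsine figures. Fisher's test is lower: at h = 0.66 it has about 58% to 72% for control prevalences from 20% to 90%.

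The cost is wording only, since the values are already scheduled at both visits. The measured-value results will not map one-to-one onto the Fried points; keeping the binary results beside them covers that.

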## Discussion

3

The FIERCE trial is the first exercise oncology study focusing on clinical and molecular analyses related to patients with mPCa during ADT treatment. The FIERCE trial employs a comprehensive analysis of the side effects of ADT treatment, assessing frailty and sarcopenia through questionnaires, physical evaluation, and imaging tests. In addition, muscle biopsies and plasma/serum will be used to evaluate biomarkers of the effects of exercise on frailty and sarcopenia. Potential modulating agents of physical exercise released by muscle cells will be examined on the LNCaP cell line, a human prostate cancer cell line that exhibits androgen-sensitive growth.

Men with mPCa undergoing treatment with ADT present with, among other side effects, loss of muscle mass, sarcopenia, and frailty, with a consequent increase in the risk of mortality (3, 4, 8). The reduction in muscle mass and frailty induced by ADT treatment has been an important clinical issue in patient management (63). In this regard, evidence supports the association of exercise-based interventions with global health improvements in patients undergoing ADT treatment with or without a diagnosis of metastases (10–12). Research has supported the feasibility and safety of physical exercise in men with metastatic or advanced prostate cancer (64–67). For example, in patients with advanced prostate cancer receiving ADT and patients with bone metastases, exercise training was able to increase muscle mass, strength, and aerobic capacity (67–70). Interestingly, Houben et al. (68) demonstrated that resistance exercise effectively countered ADT-induced side effects, regardless of protein supplementation combined with resistance exercise. Therefore, the beneficial effects of exercise among men with prostate cancer are mainly related to increased physical fitness (13) and reduced fatigue (71). Improvements in sexual and mental well-being (72, 73), as well as in quality of life (13, 74), have also been reported. However, some studies have shown no effect of exercise on sexual function (65) or quality of life (67, 75). Although these beneficial effects have been demonstrated across different training protocols and exercise types, multicomponent exercise-based training with a periodized prescription is promising for older adults and men with prostate cancer (69, 76).

Prior work has suggested that multicomponent exercise has significant potential to reduce ADT-induced side effects. In prostate cancer patients undergoing ADT, a combination of aerobic and resistance exercise enhances aerobic fitness and muscle strength, reduces fatigue, and preserves or increases lean mass, contributing to an increase in physical function and quality of life (69, 74, 77, 78). Furthermore, the addition of balance and flexibility exercises is particularly beneficial for older men with prostate cancer, to improve joint mobility, balance, and reduce the risk of falls (3). Above all, the maintenance or increase in muscle strength and mass, as well as the reduction in sarcopenia and frailty, is directly associated with a lower risk of mortality in men undergoing ADT treatment, regardless of cancer type (4, 7–9). Although multicomponent exercise may uniquely improve several components of health-related physical fitness in patients undergoing ADT treatment, the effect of multicomponent exercise on biochemical variables is poorly investigated. In this regard, Cormie et al. (77) observed a reduction in high-density lipoprotein (HDL), while Galvão et al. (69) observed a decrease in C-reactive protein, but in general, research has not identified changes in biomarkers of lipid and glucose metabolism (69, 77) or PSA concentrations (69, 74, 77, 78). Therefore, despite the beneficial effects of exercise training in men with prostate cancer, it remains unclear its impact on biochemical markers of metabolism or how exercise could modulate molecular pathways capable of mitigating the side effects of ADT treatment.

Potential molecular mechanisms that explain the beneficial effects of exercise on frailty and sarcopenia in men with mPCa are associated with low-grade inflammation (25). Conversely, changes in immunity favoring pro-inflammatory signaling are directly related to frailty (24). High levels of C-reactive protein have been consistently reported as biomarkers of frailty in older adults (79, 80). Corroborating, Navarro-Martínez et al. (5) showed that the concentrations of IL-6, C-reactive protein, and fibrinogen were positively associated with frailty in men with prostate cancer undergoing ADT. Interestingly, the authors reported that physical activity was also associated with frailty biomarkers. C-reactive protein and fibrinogen had higher serum concentrations in patients with moderate or light physical activity of <150 min per week (5). In addition, IL-6 was also higher in patients with lower walking speeds (5). Corroborating with frailty biomarkers, studies on the role of myokines in muscle tissue are still limited (28). Evidence has supported that myonectin and FGF21 were related to mitochondrial function and biogenesis (28, 81), SPARC, and brain-derived neurotrophic factor (BDNF) to muscle repair (82, 83), while increased muscle mass is associated with decorin, irisin, and FGF21 (84–86).

Moreover, the literature acknowledges the antitumor effects of exercise through myokines, particularly highlighting IL-6, IL-15, IL-10, SPARC, myostatin, irisin, decorin, and oncostatin M (87, 88). Kim et al. (89) demonstrated an increase in OSM but not SPARC and decorin after twelve weeks of exercise in prostate cancer patients treated with ADT. They used serum from these patients for *in vitro* testing, demonstrating that DU-145 prostate cancer cells had reduced proliferation when cultured with serum from trained patients (89). Similarly, using serum from prostate cancer patients who trained for 6 months reduced the proliferation of DU-145 cells. Myokine tests showed an increase in OSM and SPARC, while IGF-1 or IGFBP-3 remained unchanged after training (90). These antitumor effects have also been demonstrated using exogenous myokines. Investigation with PC-3 metastatic prostate cancer cells revealed that exogenous irisin reduced cell viability, while tumor growth and progression were reduced *in vivo*, suggesting that apoptotic pathways were enhanced by irisin (91). It was also demonstrated that exogenous decorin inhibited the growth of androgen-independent (PC3 and DU-145) and androgen-dependent (LNCaP) prostate cancer cells. In addition, the animal model treated with decorin showed delayed tumor development (92). However, research on the impact of myokines on prostate cancer is incipient, and the potential of myokines released from exercise with antitumor effects is still unclear. Furthermore, the molecular mechanisms by which exercise may contribute to the delay in muscle mass loss or gain related to ADT treatment or the impact of multicomponent exercise on cellular factors released by muscles still require further investigation and thus will be investigated in the FIERCE trial.

In this regard, the strengths of our study include the randomized controlled design and a comprehensive set of frailty and sarcopenia measures, including the utilization of muscle tissue biopsies to assess the impact of multicomponent exercise on molecular markers associated with sarcopenia. We also want to acknowledge that our study has several limitations. While the intention is to recruit frail and pre-frail participants as defined by the FRAIL questionnaire, this questionnaire is self-reported by the participant and may lead to misclassification. Although our intervention period allows us to determine changes in frailty and sarcopenia, this period would not permit us to determine if our intervention may be associated with reductions in comorbidities, metastatic modulation, or mortality. The partial clinic-based setting of the intervention may not be replicable in other environments, e.g., community programs and telehealth.

